**Assessments**				
UWES-9	x	x	x	x
BAUA-Scales	x	x	x	x
HoT-specific questionnaire of HoT staff only		x	x	x

Abbr.: *UWES-9* Utrecht Work Engagement Scale, *BAUA* Bundesanstalt für Arbeitsschutz und Arbeitsmedizin (Federal Institute of Safety at Work and Occupational Medicine)

### External validity and transferability

Since this trial is funded by German health insurance companies (“the Federal Joint Committee”), the potential transfer of HoT to the regular standard of care within the German health care system is of particular interest. An assessment of the transferability and external validity of the data will be carried out within this project using the data of the web-based German National Competency Network (“Kompetenznetz Anorexie-Register e. V.”), which contains the clinical data of children and adolescents, treated as inpatients at 16 mostly tertiary care hospitals specializing in ED treatment in Germany [55]. The HoT-data and the registry data will be compared regarding admission data to estimate the proportion of patients with AN in Germany who might be eligible for HoT. Careful interpretation will consider the non-randomized nature of such a comparison.

### Premature termination of the trial

The entire project may be terminated prematurely if patient inclusion is insufficient, or if the risks of the project outweigh the potential benefits, in that the safety and well-being of the participating patients cannot be guaranteed.

### Adaptations due to the COVID-19 pandemic

The study was planned prior to the COVID-19 pandemic. To meet restrictions (e.g., quarantines in the case of a COVID-19 infection), an adjustment had to be made to the protocol. Video consultations could replace home visits in the case of a COVID-19 infection for a maximum of 14 days.

### Strategies to improve adherence to interventions

#### Professional team

To monitor and improve adherence to the HoT intervention at the different treatment centers, all staff who work in the HoT arm received training from the coordinating physician of Aachen. In addition, each profession (e.g., nutritional therapist, nurse, etc.) was trained by the head of the respective field in Aachen. Additionally, to ensure adherence, at least yearly in-person meetings of the Aachen coordinating clinician are held with the treatment team of each site, in addition to regular biweekly supervision and exchange with the clinicians in charge at each center.

#### Families/patients

The treatment sessions are arranged with the family a week ahead of time. Patients or carers may receive additional appointments depending on their individual needs. In addition, to improve adherence, families and patients have the possibility of calling members of the treatment team during the day and the child and adolescent psychiatrist on call outside working hours. In the case of a crisis, a short-term hospitalization is possible at all sites to ensure patient and family adherence and safety.

### Outcomes

#### RCT

All outcomes of the RCT are assessed at five time points: (1) at hospital admission (T1), (2) at randomization (HoT/ TAU; T2), (3) at discharge (T3), (4) at 9 months after admission (interview by phone, T4), and (5) at 12 months after hospital admission (T5). Clinical interviews and examinations are conducted in person by experienced, trained, and (if necessary) certified medical doctors or psychologists, while self-report questionnaires are administered via the online tool “SoSci-Survey”, so that data entry and associated errors or missing values can be avoided. See Fig. 3 for a schematic diagram of the schedule of enrollment, interventions, assessments, and measures of the RCT and patient data.

##### Primary outcome

The primary outcome is the BMI (kg/m^2^) 12 months after hospital admission, which is assessed by staff blinded to the treatment allocation. The BMI is the most relevant indicator of long-term treatment success in adolescents with AN and has been used as the primary endpoint in many treatment studies [28, 56, 57]. BMI is calculated for all assessment time points from the measured height and weight of the patient in his or her underwear (except for self-reported values at T4, the interview via phone). Age- and sex-specific percentiles, SDS and %Expected Body Weight (%EBW) are calculated based on the large German reference dataset from the KIGGS study [58]. Recent studies have demonstrated that BMI alone might not be a meaningful prognostic indicator of a good long-term outcome in AAN [59]. Since randomization is stratified for BMI at admission (percentile < 10 vs. ≥ 10) and statistical analyses will be adjusted for BMI at admission and premorbid BMI, we still consider the increase in BMI to be a valid primary endpoint.

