## Methods: assignment of interventions

### Randomization and blinding

Randomization is carried out as block randomization using computer-generated random numbers, stratified by center, sex-, and age-specific BMI percentiles at admission (two strata: < 10th percentile vs. ≥ 10th percentile) at a ratio of 1:1 to the two treatment arms. Randomization lists were prepared by the Institute of Medical Informatics and Statistics at Kiel University ([name]. [name]). The randomization sequence is transferred to the participating treatment centers in sequentially numbered, sealed envelopes separately for each center-specific stratum (sex and age- and sex-specific BMI percentiles). Randomization in either the HoT arm of the study or the TAU arm takes place 1 week (± 2 days) before the start of the differential treatment, i.e., at the latest in the 7th week of IP. This time lag is necessary for organizational issues (e.g., parents taking time off from work, communicating with the school). If the patient meets the inclusion criteria for HoT after 4 to 7 weeks of inpatient treatment (and he or she included in the trial), the allocation is determined by having the approved staff at the treatment center open the respective envelope and communicate the news to the patient, family, and treatment team. Blinding of participants or study staff is not possible due to the nature of the treatments. However, a member of the staff who is assigned to another work area and who is not involved in any of the treatments assesses the clinical variables and conducts the interviews. Moreover, the BMI (weight in one’s underwear and height), an objective parameter, is used as the primary endpoint; a staff member who is blinded to the patient’s study arm (single-blind) assesses and records it.

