### Statistical methods

#### RCT

The superiority of the HoT arm over the TAU arm will be analyzed for the primary endpoint (BMI 1 year after admission) using a linear mixed model for repeated measures in which study arm, sex, BMI at admission and at randomization, and age are included as fixed effects, and center and subject ID are included as random effects. All assessments of BMI after randomization (at discharge and at the 9- and 12-month follow-up timepoints) are considered repeated outcomes (the dependent variable); thus, time point is also included as a fixed effect. The difference between the achieved BMI in both study arms at the 12-month follow-up is the parameter of interest. Re-admissions are considered intercurrent events [62] and are handled depending on the timing of readmission. For patients who were readmitted to IP due to an eating disorder during follow-up and who were still in in- or day-patient treatment at the time of the 12-month follow-up assessment or discharged within the 4 weeks prior, we will use the BMI at readmission instead of that at follow-up to obtain a conservative estimate of their BMI. A subgroup analysis for patients with AAN (admission BMI ≥ 10th percentile) will be performed for the primary outcome. In addition, (serious) adverse events ((S)AEs) are tabulated by study arm and in relation to treatment as assessed by the investigator. No statistical tests will be performed for (S)AEs. Secondary endpoints are investigated with analogous logistic, linear or time-to-event (for time to readmission) models, depending on the type of endpoint.

The statistical evaluation of the RCT is carried out according to the intention-to-treat principle: all randomized study participants are included in the statistical analysis, regardless of whether the treatment was completed. In addition, an analysis only of patients treated in accordance with the protocol—i.e., without relevant protocol violations (per protocol set)—will be performed as a sensitivity analysis for the primary outcome. In general, the mixed model for repeated measures analysis can also be applied if some of the outcome data are missing. Further sensitivity analyses considering missing values will be performed.

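### Self-reported 9-month BMI is an outcome in the primary model, and the listed terms do not confine the estimate to the measured 12-month BMI

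*Protocol article*

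**What the plan says.** Under Primary outcome, the protocol article states: "The primary outcome is the BMI (kg/m^2^) 12 months after hospital admission, which is assessed by staff blinded to the treatment allocation". The same section says that BMI comes from measured height and weight at all time points "except for self-reported values at T4, the interview via phone". T4 is the 9-month contact.

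Under Randomization and blinding, the article says that participants and study staff cannot be blinded. Its answer to this is that BMI, "an objective parameter, is used as the primary endpoint; a staff member who is blinded", is recorded by that person. It also says that interviews are held by someone who takes no part in the treatments.

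Under Statistical methods, RCT, the primary analysis is a linear mixed model. Its fixed part is listed thus: "study arm, sex, BMI at admission and at randomization, and age are included as fixed effects". Time point is added as a further fixed effect. The random part is described separately: "center and subject ID are included as random effects". On the outcome it says: "All assessments of BMI after randomization (at discharge and at the 9- and 12-month follow-up timepoints) are considered repeated outcomes". On the target it says: "The difference between the achieved BMI in both study arms at the 12-month follow-up is the parameter of interest". No arm-by-time term is listed, and T4 is not handled differently from the measured visits. Sensitivity analyses for missing values are announced, but none is named for self-reported BMI.

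**The concern.** The article's protection against open-label bias rests on a measured value recorded by a blinded assessor. That protection covers the 12-month BMI. It does not cover T4, where the patient supplies the number and knows the arm. The Introduction describes fear of weight gain and the influence of weight on self-worth as core features of this disorder, so self-reported weight is a weak form of this particular outcome.

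Whether this matters for the primary result depends on how much T4 can influence the 12-month estimate. That turns on one term the article does not list. A model with arm and time as main effects estimates a single arm difference averaged over T3, T4 and T5, and in that average T4 counts directly. A model with an arm-by-time interaction gives T4 its own arm difference and leaves the 12-month difference to the 12-month data, apart from patients whose 12-month value is missing. If arms differed in reporting error, the first model would carry that error into the primary estimate, and nothing in the fit would reveal it.

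**Working it through.** **Inputs from the article**
- Planned difference at one year: 3.6 − 3.0 = 0.6 kg/m² (Sample size and recruitment).
- Missing primary endpoint: about 10% (same section).
- Outcomes T3, T4, T5; fixed arm and time; random subject intercept (Statistical methods, RCT).

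**Assumed, not in the article**
- Between-arm difference in mean T4 reporting error: b = 0.3 kg/m², with 0.5 and 1.0 for range.
- Within-patient correlation ρ between visits: 0.3 to 0.85 in step 1, 0.5 to 0.85 in steps 2 and 3.

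The article states no weight for T4, so there is no figure of its own to reproduce.

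**Step 1. Terms as listed (no arm-by-time)**

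With complete data the common arm effect weights the visits by w = V⁻¹1 / (1′V⁻¹1), where V is the covariance of the three outcomes. A random subject intercept makes V compound symmetric. Then w = (1/3, 1/3, 1/3) at any ρ, and the shift in the estimate is b/3.

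| b (assumed) | Shift | Share of 0.6 |
|---|---|---|
| 0.3 | 0.10 | 17% |
| 0.5 | 0.17 | 28% |
| 1.0 | 0.33 | 56% |

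Under an AR(1) covariance, which the article does not describe, the T4 weight would fall from 0.26 (ρ = 0.3) to 0.07 (ρ = 0.85).

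**Step 2. Arm-by-time interaction, contrast at T5**

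With complete data T4 has zero weight in the T5 contrast. With a fraction m missing T5, the arm mean at T5 is the mean of those observed plus a correction from T3 and T4. The shift is m × β₄ × (b among those missing T5 − b among those observed), where β₄ is the coefficient of T4 when T5 is predicted from T3 and T4.

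- Uniform misreport within an arm: the bracket is 0, so the shift is 0.00 at any m.
- Misreport of 0.3 only in those missing T5, m = 0.10, compound symmetry, β₄ = ρ/(1 + ρ):
  - ρ = 0.5: 0.10 × 0.333 × 0.3 = 0.010
  - ρ = 0.85: 0.10 × 0.459 × 0.3 = 0.014
- Same case under AR(1), β₄ = ρ:
  - ρ = 0.5: 0.10 × 0.50 × 0.3 = 0.015
  - ρ = 0.85: 0.10 × 0.85 × 0.3 = 0.026

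The range at 10% missing is therefore about 0.01 to 0.03 kg/m², at most 0.026/0.6 = 4% of the planned difference.

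**Step 3. Price of leaving T4 out, with the interaction in place**

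The variance of the T5 mean is proportional to (1 − R²)/(1 − m) + R², where R² is the share of T5 variance explained by the earlier visits in the model. For ρ = 0.7 and m = 0.10:
- Compound symmetry: R² is 0.576 with T3 and T4, 0.490 with T3 only. Variances 1.047 and 1.057; standard error ratio 1.005.
- AR(1): R² is 0.490 and 0.240. Variances 1.057 and 1.084; standard error ratio 1.013.

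Across ρ = 0.5 to 0.85 the ratio is 1.003 to 1.013, so the loss is about 1% or less.

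**The case against.** The strongest reply is that the one-third weight belongs to a reading that the article itself undercuts. It names the 12-month difference as the target, and a main-effects model cannot produce a difference specific to 12 months. A statistician implementing the plan would probably add the interaction, and the analysis plan may already contain it. A reader might infer that the article gives T4 the same weight as the blinded measurement; it assigns no weights at all. This part of the reply stands. What remains is that the listed terms and the stated target do not fit together, and that the influence of the self-report depends on how the mismatch is resolved.

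A reader might also infer that home treatment teaches families to monitor weight, so that reporting errors must differ by arm. The article describes support with refeeding, food intake and exercise, not weighing at home. It also instructs parents on meals during stabilization, before randomization. By its own durations (5–8 plus 12–16 weeks), planned home treatment ends 17 to 24 weeks after admission, well before month 9. Differential misreporting is possible but undocumented.

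Nor is there a contradiction with the blinding claim. Blinded recording is claimed for the primary endpoint at 12 months, the T4 exception is disclosed, and the interviewer is not a treating clinician. Being aware of the arm applies to the patient who reports the value.

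Finally, deleting T4 outright can be disputed. For patients with T4 but no T5 it is the only BMI after discharge, and dropping it weakens the missing-at-random assumption. Under the main-effects model, deletion would not restore the target either: T3 would then carry half of the estimate. That is why the contrast has to be settled first.

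**Conclusion.** The point holds in a limited form. A self-reported value from patients who know their arm is an outcome in the primary model beside measured BMI, and the article names no safeguard for it. With the terms as listed, T4 carries about one third of the arm effect, and an assumed 0.3 kg/m² between-arm misreport shifts the estimate by 0.10 kg/m², 17% of the planned 0.6. With an arm-by-time term and the contrast at T5, the shift is 0.00 for a uniform misreport and about 0.01 to 0.03 kg/m² if the misreport is confined to the roughly 10% missing T5.

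These figures rest on a random-intercept covariance and complete data for the one-third weight, on the assumed correlations, and on an assumed misreport. It would go too far to read 17% (or the 28% and 56% for larger assumed errors) as the bias to be expected: the document gives neither direction nor size for differential misreporting, and the larger shifts vanish under the model that matches the stated target. The required sample size is unaffected, since it was planned on the one-year difference alone.

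**What to change.** In Statistical methods, RCT, make two changes.

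1. Add the arm-by-time interaction to the fixed effects, and define the primary estimate as the arm contrast at T5. T4 then informs it only through patients missing T5.
2. Pre-specify, as a named analysis, the same model fitted to measured BMI only (T3 and T5, contrast at T5). Otherwise use the T4 self-report only as auxiliary information for missing T5, for example in multiple imputation.

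The cost is a sentence or two of text and one extra model fit. The measured-only fit has a standard error about 1% larger at 10% missing T5, and it gives up the only post-discharge BMI for patients who have T4 but no T5. The T5 contrast is also less precise than an arm effect pooled over three visits. For example, at an assumed ρ = 0.7 the pooled variance is (1 + 2 × 0.7)/3 = 0.80 of the single-visit variance, so the standard error of the T5 contrast is 1/√0.80 = 1.12 times as large. The pooled effect, however, is not the stated target.

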##### Secondary outcomes

Figure 3 shows all secondary outcomes (all at T5), e.g., ED symptoms and severity, other psychiatric comorbidities and quality of life, and all assessment instruments.

#### Cost analysis

Regarding the cost analysis, the direct costs of treatment (TAU vs. HoT between randomization and discharge) are collected from the centers.

#### Implementation and staff appraisal

For the descriptive implementation and feasibility analysis, treatment data are collected at each site: numbers of all AN patients screened, those who meet the inclusion criteria and are willing to participate in the study, the proportions of patients who were successfully stabilized and able to start and finish HoT according to the treatment plan, and the proportions of patients who do not meet the requirements for HoT, are analyzed. In addition, a descriptive evaluation of the actual weekly treatment implementation is carried out: the number of treatment sessions by the different occupational groups over the course of the HoT and the number of cancelled home visits. To assess the staff’s appraisal of HoT and the work satisfaction and stress of both groups (HoT/TAU), staff members of both treatment teams complete the short version of the Utrecht Work Engagement Scale, (UWES-9, [60]) and the “Bundesanstalt für Arbeitsschutz und Arbeitsmedizin” (Federal Institute of Safety at Work and Occupational Medicine)-Scales (BAUA-Scales, [61]). In addition to the validated questionnaires on work satisfaction and stress, a short debriefing is also designed for the therapists of the HoT team only. This questionnaire explicitly debriefs on stress and satisfaction with this specific new treatment. Table 3 displays the assessments of the staff.

#### Transferability

See above, 2.D.

##### Sample size and recruitment

The data of the HoT pilot study (*n* = 22) [31], the ANDI study (*n* = 172) [28], and the German Competence Network AN Register e.V. (*n* = 289) [55] were used as the basis for the statistical sample size planning of the RCT. In the IP arm, an increase in BMI of approximately 3 kg/m^2^ (SD 1.8) is expected after 1 year (ANDI study, [28]), and, in the HoT arm, an increase of 3.6 kg/m^2^ (SD 1.5; HoT pilot study) is expected. This translates to a standardized effect size of Cohen’s *d* = 0.47. For a statistical power of 80% (5% significance level), a sample size of 74 evaluable patients per study arm is needed. To account for approximately 10% loss-to-follow-up (missing values for the primary endpoint) [28], we plan to randomize 164 patients. Based on the experience of the pilot study, in which one third of the patients initially included at admission did not fulfill the criteria for transfer to HoT after 4 to 7 weeks of inpatient stabilization [31], a total of approximately 240 patients needs to be included in the study upon admission. To publicize the study, leaflets explaining it (reviewed and accepted by the respective ethics committees) are distributed regularly to general and pediatric practices as well as registered doctors and psychotherapists. Additionally, the consortium has its own website and email contacts and videos explaining the study. In addition, we give talks to local medical doctors and psychotherapists to explain the project.

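### The effect size d = 0.47 does not follow from the printed means and SDs, which give 0.36; on those inputs 74 evaluable patients per arm have about 59% power, not 80%

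*Protocol article*

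**What the plan says.** The calculation is in the protocol article under Sample size and recruitment. For the inpatient (TAU) arm, "an increase in BMI of approximately 3 kg/m^2^ (SD 1.8) is expected after 1 year", taken from an earlier trial of day patient treatment. For the home treatment arm, "an increase of 3.6 kg/m^2^ (SD 1.5; HoT pilot study) is expected". The next sentence gives the result: "This translates to a standardized effect size of Cohen’s *d* = 0.47". The sample size follows from it: "For a statistical power of 80% (5% significance level), a sample size of 74 evaluable patients per study arm is needed". With about 10% loss to follow-up, "we plan to randomize 164 patients", that is, 82 per arm at 1:1 allocation.

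The section mentions no covariate adjustment, correlation or other SD, and does not say whether the 5% level is one- or two-sided.

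**The concern.** All the inputs and the result stand within a few lines of each other, and they disagree. A reader who divides the difference of 0.6 by either stated SD gets 0.33 or 0.40, and any averaged SD gives something in between. The stated 0.47 lies outside that range.

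This is the only power justification in the article for the primary endpoint of a superiority trial whose results are meant to inform routine care and insurance coverage. If the printed inputs are the real planning assumptions, the trial would miss its own expected effect about 4 times in 10, yet a null result would be read as coming from a trial with 80% power.

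**Working it through.** **Inputs** (all from Sample size and recruitment): gains 3.0 and 3.6 kg/m²; SDs 1.8 and 1.5; d = 0.47; power 80%; α = 5%, taken as two-sided because the text does not say; 74 evaluable per arm; 10% loss; 164 randomized.

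**1. From d to n: this step reproduces.** With n = 2(z₀.₉₇₅ + z₀.₈₀)²/d² and d = 0.47, n = 2(1.960 + 0.842)²/0.2209 ≈ 71.1, so 72 per arm (73 with the t-test). The stated 74 is within two patients, and power at 74 per arm is 81%.

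**2. From n to the number randomized: no problem.** 74/0.9 = 82.2, and 82 × 0.9 = 73.8. Two arms of 82 give 164.

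**3. From means and SDs to d: this step does not reproduce.**

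Pooled SD = √((1.8² + 1.5²)/2) = √((3.24 + 2.25)/2) = 1.657

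d = (3.6 − 3.0)/1.657 = 0.362

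| SD used | d | Power at 74 per arm | Evaluable per arm for 80% |
|---|---|---|---|
| 1.5 alone | 0.400 | 68% | 100 |
| Pooled, 1.657 | 0.362 | 59% | 121 |
| Weighted by source study sizes (172 and 22), 1.770 | 0.339 | 54% | 138 |
| 1.8 alone | 0.333 | 52% | 143 |
| Stated in the plan | 0.47 | 81% | 73 |

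Power is from the noncentral t distribution, two-sided 5%. A Welch test with the two SDs kept separate also gives 59.0%.

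**4. Does rounding explain it?** If all four inputs, with the inpatient gain read as 3.0, are pushed to their most favourable one-decimal limits, d = (3.65 − 2.95)/√((1.75² + 1.45²)/2) = 0.436, still below 0.47.

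**5. Does a one-sided test explain it?** At one-sided 5% and d = 0.362, power at 74 per arm is 71%, and 95 per arm would be needed.

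**6. What would give 0.47?** Any one of these:
- a difference of 0.47 × 1.657 = 0.779 kg/m², that is, an inpatient gain of 3.6 − 0.779 ≈ 2.82;
- a common SD of 0.6/0.47 = 1.28, below both stated SDs;
- covariates explaining R² = 1 − (0.362/0.47)² = 0.41 of the variance (r ≈ 0.64).

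**7. What can 74 per arm detect?** For 80% power with the t-test, d must be 0.464, which is 0.464 × 1.657 ≈ 0.77 kg/m².

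**The case against.** Two points on the other side carry weight.

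First, the inpatient gain is printed only as approximately 3, without a decimal. If that is rounded to a whole number (an assumption), the true value could lie anywhere from 2.5 to 3.5, and d at the pooled SD from 0.66 down to 0.06, a range that includes 0.47. An unrounded 2.8 gives d = 0.48 and 83% power at 74 per arm. In that case d, 74 and 164 would all be right and only the printed mean would be imprecise.

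Second, 59% is the power of an unadjusted t-test. Under Statistical methods, the primary analysis is a mixed model adjusted for BMI at admission and at randomization, sex and age. If the gain is counted from admission, part of it comes before randomization and is captured by a covariate. Assumed correlations of 0.3, 0.5, 0.6 and 0.64 give power of 63%, 71%, 78% and 81%. The article gives no correlation, and if the SDs are those of change scores, some of this benefit is already used.

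Both points stand as possible explanations and limit how the 59% should be read. Neither removes the error: the sample size section invokes neither, and says that the printed values themselves lead to 0.47. Nor is this a detail left to a longer document, since the article prints inputs and result together. It cannot settle whether the slip is in d or in a rounded input.

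**Conclusion.** The point holds. The printed means and SDs give d = 0.36 (0.33 to 0.40 across the stated SDs, with the inpatient gain taken as 3.0), not 0.47. On those inputs, with an unadjusted two-sided 5% test, 74 evaluable patients per arm have about 59% power. Reaching 80% would take 121 evaluable per arm, or about 135 randomized per arm at 10% loss (121/0.9 = 134.4), against 82 planned.

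The 59% is the power on the plan's printed assumptions. The power of the adjusted analysis may be higher, but it cannot be worked out from the article. The power statement must be corrected because the trial's size rests on it.

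**What to change.** Correct the sample size paragraph, without enrolling more patients, in one of two ways:

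- **If 0.47 came from unrounded means or an adjusted SD:** print those inputs (an inpatient mean of about 2.82, or a residual SD of about 1.28 with R² of about 0.41 and its source) and derive 74 from them.
- **If it did not:** state d = 0.36, power of about 59% for a difference of 0.6 kg/m², and 80% power for about 0.77 kg/m² at 74 evaluable per arm.

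In either case, state whether the 5% level is one- or two-sided. The cost is one paragraph in the protocol, and in the SAP if it repeats the figure. Under the second route the stated power becomes less favourable. The correction should be made before the results are interpreted, so that a null finding is read against the right power.
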